## Abstract

**Highlights:**

**What are the objectives of the study protocol?**
To describe methods to test the acceptability and feasibility of a digital intervention promoting flourishing in early childhood.To describe methods to collect and analyse pilot data measuring changes to parental self-efficacy.

**What are the anticipated implications of the main finding?**
Findings will inform a future trial testing the effectiveness of the Flourishing Intervention.We anticipate that the findings will support the acceptability and feasibility of the intervention.

**Abstract:**

Background: Globally, rates of children with physical and mental health problems are increasing. Health issues in early childhood often persist into adulthood, highlighting the need to ensure children are supported to flourish from the start of life. Objectives: This protocol describes methods used to test the acceptability and feasibility of a novel digital Flourishing Intervention (designed to empower parents and promote child wellbeing), comprising a Flourishing Check (a newly developed online questionnaire) and a Pathway Tool (an online directory of high-quality, evidence-based programmes and resources). Methods: Using a randomised feasibility trial, participants (N = 600 parents of children aged 0–5 years) will complete the Flourishing Check. The intervention group (n = 400) will access the Flourishing Check and Pathway Tool, whereas a waitlist control group (n = 200) will access the Flourishing Check only. Results: The primary aim is to assess the acceptability and feasibility of the intervention through a mixed-methods design incorporating quantitative data from pre- and post-intervention questionnaires and qualitative data from focus groups. This will be assessed using a traffic light system, which will inform if and how to proceed to a future effectiveness trial. Secondary aims are to assess changes in parent and child outcomes. Primary outcomes will be assessed using descriptive statistics and thematic analysis. Secondary outcomes will be analysed using mixed-effects regression models. Conclusions: We anticipate that the Flourishing Intervention will be feasible and acceptable to parents. This trial is registered with the Australian New Zealand Clinical Trials Registry (ACTRN12626000187347).

## 1. Introduction

Supporting childhood mental and physical health in the early years (0–5 years) has been identified as a global research priority [1,2,3,4,5,6,7]. Mental health issues that develop during early childhood often persist into adulthood, preventing children from realising their potential and increasing long-term burden on families, economies, and health systems [2,8]. Insufficient support for this age range is a missed opportunity, as this is when developmental plasticity is at its peak [9].

Understanding when and how to access early intervention can be challenging for parents and caregivers [10] (hereafter referred to as “parents”). The World Health Organization (WHO) recommends developmental screening during children’s visits to health services in the first five years of life [11] as a window of opportunity to initiate early intervention. However, in Australia, disparities in access reduce attendance, and there is little nationally representative data on the uptake of these services [12]. The proportion of eligible children attending their free universal two-year child health checks in metropolitan WA is only 30% [13]. Families are underutilising these screening opportunities and cite a lack of awareness of the programmes and services available to them [14]. Parents need accessible pathways to navigate healthcare systems [15] but frequently feel overwhelmed by information and disempowered [10].

### 1.1. The Value of Digital Health Interventions in the Early Years

Digital interventions for early childhood aim to improve access to credible and evidence-based supports, parent and child wellbeing, and provide targeted pathways to intervention and prevention [16]. They have the potential to improve child and parent outcomes and are more accessible and cost-effective than face-to-face interventions [16,17,18]. Online interventions have been shown to reduce child problem behaviour and improve parental mental health [19]. Furthermore, online parental support has been shown to be non-inferior to face-to-face support in improving child and parent mental health, and more satisfactory to parents [20,21,22]. However, further research is needed to improve parental adherence to these interventions [23,24] and improve long-term benefits [16]. Given the importance of intervening early (i.e., in early childhood) [9] and the cost-effectiveness and scalability of digital interventions, their development and evaluation represent a research priority. Importantly, digital interventions to improve early childhood must be co-designed with and by intended users to ensure resulting interventions address their needs [25]. Co-design refers to the active involvement of stakeholders (e.g., end-users, service providers) in the development and implementation of solutions to pre-defined problems [26]. Meaningful co-design is maintained throughout all project stages, emphasises respect and collaboration, and is essential to the design of acceptable and feasible solutions [26,27,28]. Improving health outcomes for young children therefore relies on empowering parents and caregivers.

### 1.2. Flourishing in Early Childhood

Flourishing is a state of positive functioning in all areas of life, characterised by the presence of strengths or protective factors and the absence of symptoms and disease [29,30,31]. It goes beyond quality of life and wellbeing to encompass additional individual factors, including happiness and relationships, and environmental factors such as strong communities [31,32]. Recent reviews have concluded that there is dissensus among conceptualisations of flourishing in early childhood (0–5 years), and there is a need to develop frameworks and measures addressing this gap [32]. To define and operationalize early childhood flourishing, the current authors engaged community stakeholders (e.g., parents, early childhood professionals, and children) to understand what it means to them [10]. Responses were collected through self-report questionnaires, focus groups, and interviews with children, and analysed using a mixed-methods approach. This resulted in a community-informed framework comprising five domains of early childhood flourishing: physical safety, love and family, positive lifestyle, physical and mental health, and fun and happiness.

Additionally, key barriers and enablers to supporting early childhood flourishing were identified. Key barriers included time scarcity, competing commitments, and the cost and difficulty of securing appointments. Enablers included family support (e.g., extended family and friends), safety (physical and online), good health and nutrition, and sleep. Parents voiced concerns about the volume of parenting information and resources, and the lack of clarity and consensus among them. These responses suggested parents need interventions that (1) help them understand their children’s strengths and support needs (i.e., where they are flourishing and where they may benefit from support), and (2) provide targeted pathways to evidence-based supports.

Subsequently, a scoping review (under review) was conducted by the authors to assess alignment of the community-informed framework with the early childhood flourishing literature. Searches were conducted across nine databases to identify existing frameworks, measures, domains, and indicators of early childhood flourishing. Judgements of alignment were based on consensus among researchers on which domains and indicators identified in the scoping review results were theoretically linked to those in the pre-existing framework. Curiosity, learning, and engagement were identified as a gap, resulting in a revised framework comprising six domains: safety and security, love and connection, a positive lifestyle, wellbeing, fun and play, and curiosity. This framework aligns with and extends on existing flourishing frameworks such as the National Survey of Children’s Health Child Flourishing Index.

Within this framework, flourishing is conceptualised through both determinants and indicators. Certain environmental determinants (e.g., safety and security, love and connection, positive lifestyle) must be present for children to demonstrate the external indicators of flourishing (e.g., wellbeing, fun and play, and curiosity). Early childhood flourishing is therefore holistic and comprehensive, and distinct from existing constructs which are narrower in scope (e.g., wellbeing, quality of life, developmental outcomes).

There are many existing interventions that aim to reduce child problem behaviour or improve parenting skills [17,19,24]. The intervention described in this protocol sits apart from those in that it aims to prevent problem behaviours and, crucially, enhance strengths. Furthermore, it was developed through rigorous co-design, ensuring it addresses the specific needs of its intended users [10].

### 1.3. Mechanisms of Change

Sanders and Mazzucchelli [33] present a conceptual model outlining mechanisms of change by which parenting interventions lead to improved child outcomes. The primary mechanism is changes in parenting behaviours and attitudes (e.g., increased self-regulation, more positive interactions, less coercive interactions, and appropriate expectations of children and self). Within this model, parenting changes are influenced by engagement, which is in turn influenced by parental concerns (e.g., perceived need for support), wellbeing (e.g., mental health, attachment), cognitions (e.g., perceived self-efficacy), cultural and social influences, motivational contexts (e.g., anticipated child benefits), and intervention features (e.g., accessibility, format, cost, timing).

A Logic Model incorporating a theory of change is a valuable tool for visually clarifying the intended pathways to expected outcomes and long-term change in complex health challenges [34]. For this study, the research team developed a logic model for enhancing flourishing in the early years to measure and evaluate project inputs, outcomes, and impacts (see Figure 1). Additionally, pre- to post-intervention changes to parental perceived self-efficacy, confidence, wellbeing, engagement, knowledge of when and how to seek help, and perceived need for support will be explored to better understand mechanisms of change.

### 1.4. The Flourishing Intervention

In this protocol, we describe the Flourishing Intervention, designed to promote child flourishing by improving parents’ awareness of their children’s strengths and support needs, and their knowledge of when to seek support. This digital health intervention comprises a Flourishing Check and a Pathway Tool, conceptualised by the research team with the aim of providing parents with both knowledge of and access to timely supports. The design and testing of the Flourishing Intervention are nested within a longitudinal cohort study, ORIGINS, based in Perth, Western Australia. ORIGINS [35] is a collaboration between The Kids Research Institute Australia and Joondalup Health Campus, and is one of the most comprehensive studies of pregnant women and their families in Australia.

### 1.5. The Flourishing Check

The Flourishing Check is a new questionnaire designed to enable parents to check in on their child’s level of flourishing and signpost domains where they may benefit from support. The reliability of children below five years of age to self-report is limited [36]. Therefore, this assessment relies on parent-proxy reports. It is underpinned by the early childhood flourishing framework described above, uses items uncovered through the scoping review (under review) into early childhood flourishing measures, and is also underpinned by The Nest [37] (an Australian framework which outlines population-level indicators of child and adolescent wellbeing). The Flourishing Check is available in two versions assessing flourishing in distinct developmental stages (0–2 years and 3–5 years). Assessment development followed best-practice guidelines [38], starting with a large item pool and adjusting/narrowing down the items using the Delphi method of consultation with experts. The questionnaire will be checked for test–retest reliability and validated against the Paediatric Quality of Life questionnaire (PedsQL) and the Ages and Stages Questionnaire–Socio-Emotional scale (ASQ-SE). A manuscript detailing the development and psychometric properties of the Flourishing Check is currently in preparation.

### 1.6. The Pathway Tool

The Pathway Tool is a digital information hub through which parents can find high-quality, evidence-based programmes and resources that support early childhood flourishing. Based on their responses to the Flourishing Check, the Pathway Tool website will signpost parents to specific domains of flourishing where their child may benefit from support and direct them to relevant, evidence-based programmes and resources. Figure 2 shows a screenshot of the Pathway Tool homepage. The Pathway Tool was developed by the project team in an iterative process involving a systematic search for eligible services, independent reviewers screening search results, and the application of a comprehensive quality assessment.

The Pathway Tool was primarily designed to be applicable to residents of the Joondalup and Wanneroo regions of Perth, Western Australia, as this is the location of the ORIGINS cohort [35]. Therefore, in-person programmes included in the tool will be most accessible to residents of this region. However, the tool contains resources and online content applicable to residents beyond this area (i.e., across broader Perth metropolitan regions). See Section S1 of the Supplementary Materials for further details on the development of the Pathway Tool.

### 1.7. Governance

This intervention was co-designed with stakeholders’ input at all project stages. Two groups of stakeholders have collaborated in its development and will have ongoing involvement in future project phases: (a) a Consumer and Community Advisory Committee comprising parents, early childhood educators, and community representatives, who ensured the intervention is relevant, culturally appropriate, and accessible, and (b) a Steering Committee including representatives from partner organisations representing the Australian early childhood sector, the local community, the interests of multicultural families and fathers, along with experts in digital design. Collectively, these committees have provided guidance in the form of lived experience [39], expertise in early childhood development, expertise in digital tool development, and diverse cultural perspectives. This process has resulted in an intervention that is informed by relevant knowledge and centred on the needs and priorities of intended end-users. For example, it was at the advice of these groups that the name of the Flourishing Check was changed from the original title of Flourishing Assessment (which was perceived as having a clinical/diagnostic undertone that did not align with the purpose of the questionnaire). This study will be coordinated at The Kids Research Institute Australia, with the corresponding author overseeing all aspects of trial conduct, including recruitment, consent, intervention delivery, and data collection. Data management, including data entry, storage, and quality checks, will be conducted by the research team under the supervision of the corresponding author. Given the low-risk, short-duration, single-site nature of the study, no separate endpoint adjudication committee or independent data management team has been established.

### 1.8. Aims

The primary aim of this study is to test the acceptability and feasibility of the Flourishing Intervention and explore any areas for modification required. Secondary aims are to collect pilot data to explore post-intervention changes in parent and child outcomes, including (i) perceived self-efficacy in recognising and supporting flourishing in early childhood, (ii) perceived knowledge of how and when to seek support, (iii) engagement with and participation in supports relevant to flourishing in the early years, (iv) parent wellbeing, and (v) paediatric quality of life. It is hypothesised that the intervention components will be deemed feasible and acceptable to the level where this pilot can proceed to a full trial (either with or without modifications).

## 2. Materials and Methods

### 2.1. Study Design

A randomised feasibility trial will be used to test the feasibility and acceptability of a new flourishing intervention and explore any areas for modification required (primary aim). A secondary aim will be to explore whether the intervention group shows any improvements in parent outcomes relative to controls after engaging with the Pathway Tool. This protocol is reported in accordance with SPIRIT guidelines and informed by the CONSORT extension for pilot and feasibility trials (see Section S2 of the Supplementary Materials) [40].

Participants will complete a screening form to determine eligibility and then be randomly allocated to either the intervention group (which will gain access the Pathway Tool immediately after completing the Flourishing Check), or the waitlist-control group (which will continue their usual activities and only gain access to the Pathway Tool after post-test assessments are completed or the final data collection time point has closed).

Quantitative and qualitative data will be collected at five timepoints: [T1] pre-intervention (baseline); [T2] acceptability and feasibility questionnaires (intervention group only), 1 week after T1; [T3] test–retest reliability (n = 200), 2–4 weeks after T1; [T4] qualitative feedback on the Flourishing Check and Pathway Tool (*n* ≈ 30, intervention group only), 3 months after T1; and [T5] post-intervention outcome measures, 6 months after T1. See Table 1 for a summary of the research procedure.

### 2.2. Participants

Participant eligibility criteria are as follows: (1) must be a parent or primary caregiver of a child aged 0–5 years, (2) reside within the Perth metropolitan area, (3) be over 18 years of age, and (4) have reliable internet access. Parents who meet these criteria will be eligible to register one child per family in the study.

This study has been approved by The University of Western Australia (UWA) Human Research Ethics Committee (HREC) (Project No. 2025/ET000152) and is registered with the Australian New Zealand Clinical Trials Registry (ACTRN12626000187347). This study is a sub-project of ORIGINS.

Participants will be compensated for their time with e-gift cards (40 AUD at T1 and 20 AUD at all other timepoints). Focus group participants will be compensated 50 AUD per hour. Participants will receive an email prompt to complete outcome measures at six months’ post-intervention [T5] and will receive reminders after one and three weeks of non-completion. Participants who have not completed the questionnaires at T2 and T5, two weeks after the second reminder, will be marked as incomplete.

Participant communications will emphasise that the intervention is under development and results are not diagnostic. Phone numbers for support services will be provided to alleviate any concerns parents may have after completing the Flourishing Check. We do not anticipate any other unintended harms.

#### 2.2.1. Recruitment

A link to an Expression of Interest (EOI) will be sent to ORIGINS participants and community members by The Flourishing Child research team and partner organisations via email. Digital and printed promotional materials will be circulated through online platforms, social media, advertising, and within the local community. The EOI will direct participants to online study information (e.g., eligibility criteria, time commitment, reimbursement). After reviewing this information, participants who wish to take part will complete a screening form and, if eligible, provide electronic informed consent. We aim to recruit participants primarily within the Joondalup and Wanneroo regions over the three-month recruitment period, but we will also accept participants in the wider Perth metropolitan area.

Participants will access the intervention via personal devices. After eligibility screening, all participants will be randomly assigned to either a waitlist-control or intervention group using REDCap’s randomisation module, ensuring that assignment is concealed from researchers until after enrolment [41,42]. Randomisation will be conducted using a 2:1 allocation ratio (intervention/control), stratified by child age, gender, and locality. Participants will be notified of their group assignment and respective study involvement via email. Blinding cannot be implemented in this study, as participants would be aware of their group allocation due to the nature of the intervention; moreover, blinding is not required in this non-clinical trial context. All participants will complete a questionnaire battery at baseline. The intervention group will gain access to the Pathway Tool after completing the Flourishing Check. On completion of the full intervention (i.e., Flourishing Check and Pathway Tool), we will ask intervention group participants to register their interest in participating in focus groups. The waitlist-control group will continue their usual activities. Once data collection has been completed, they will be given access to the Pathway Tool. For ethical reasons, waitlist control groups are preferred over no-treatment controls [43]. Recent trials testing digital parenting interventions have used waitlist controls [44,45,46]. For these reasons, a waitlist control will be used in this study.

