### 2.5. Data Screening

Data screening will be automated using formulae within REDCap’s data quality functionality. Participant records will be flagged where responses are inconsistent or contradictory, attention checks are failed, or key variables are missing responses. As an additional measure, records will be manually screened by members of the research team to validate participants. Data will be monitored by research team members throughout the recruitment and follow-up periods to ensure that (1) recruitment targets are achieved, (2) participants are reimbursed appropriately and efficiently, and (3) only valid data is included in the analysis.

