**Figure 3 children-13-00581-f003:**
[figure not shown]
Visual summary of data triangulation.

**Table 1 children-13-00581-t001:** Schedule of enrolment, interventions, and assessments.

	STUDY PERIOD							
	Enrolment	Allocation	Post-Allocation					Close-Out
TIMEPOINT	−*t* _1_	0	*t* _1_	*t* _2_	*t* _3_	*t* _4_	*t* _5_	*t_x_*

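### Parents are randomised before the T1 baseline battery and nothing withholds the arm until T1 is submitted, so self-rated baseline scores may react to allocation

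*Protocol article*

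**What the plan says.** Section 2.1 gives the order of entry: "Participants will complete a screening form to determine eligibility and then be randomly allocated to either the intervention group". Section 2.2.1 repeats it: "After eligibility screening, all participants will be randomly assigned to either a waitlist-control or intervention group". The same paragraph then says "Participants will be notified of their group assignment and respective study involvement via email", explains why blinding is not used, and continues: "All participants will complete a questionnaire battery at baseline". Allocation is concealed from researchers only up to enrolment.

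Table 1 shows the same order. Allocation sits at timepoint 0, and t1 to t5 all sit under "Post-Allocation". The t1 column holds the baseline of every parent and child outcome. It also holds the Flourishing Check acceptability and feasibility questionnaire, which is not marked as intervention-arm only.

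Section 2.5 covers validity screening: "Participant records will be flagged where responses are inconsistent or contradictory, attention checks are failed, or key variables are missing responses". Research team members also screen records by hand, and one stated purpose of monitoring is that "only valid data is included in the analysis".

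Section 2.6.2 fits models with group, time (baseline and follow-up) and their interaction. For between-group differences it also adjusts for the baseline score.

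**The concern.** A baseline measure is protected by randomisation only if it is taken before allocation, or at least before the participant learns the result. Here it is taken after allocation and possibly after disclosure. The section on limitations says that all measures except the engagement metrics are self-report or parent proxy report. Ratings of one's own self-efficacy and knowledge of supports could plausibly move when a parent learns that access comes now, or only after a wait of about six months.

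Three things are exposed:

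- **The between-arm estimates.** They use T1 twice, and adjusting for a baseline that has itself reacted to allocation does not remove the reaction. Section 3 says these results will inform effect sizes for the next trial, so bias matters even though significance is not the aim.
- **The Flourishing Check ratings.** They are collected at T1 from parents who are already allocated, and they feed two of the four rows of the progression table (Table 3).
- **The analysed set.** Screening that relies on questionnaire answers can only follow allocation. If records are removed, removal could differ by arm.

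**Working it through.** **1. Order of events, side by side**

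| Step | Source | Position |
|---|---|---|
| Eligibility screen, consent | 2.2.1; Table 1 | before timepoint 0 |
| Randomisation | 2.1; 2.2.1; Table 1 | timepoint 0 |
| Email with the arm | 2.2.1 | no day given; written before the baseline sentence |
| T1 battery and Flourishing Check | 2.2.1; Table 1 | after timepoint 0 |
| Validity screening on responses | 2.5 | after T1, hence after allocation |

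Randomisation before T1 is explicit in two sections and in Table 1. Disclosure before T1 is not explicit, but nothing rules it out. Section 2.1 labels T1 as preceding the intervention. That is true of access to the Pathway Tool, but it does not make T1 precede allocation.

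**2. The plan's own figures**

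Section 2.6.2 allows for a loss of one third: 400 × 2/3 = 267 and 200 × 2/3 = 133. It claims 80% power for d = 0.30 at alpha 0.05 (taken as two-sided) with a Mann–Whitney test.

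- Normal approximation: √(267 × 133 / 400) × 0.30 − 1.96 = 2.83 − 1.96 = 0.87, so power is 0.807.
- With the Mann–Whitney efficiency of 3/π: 2.76 − 1.96 = 0.80, so power is 0.789.

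Both agree with the stated 80%. The sequencing point does not depend on these figures. The value d = 0.30 serves below only as a yardstick.

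**3. Possible bias**

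Let s be the shift in the between-arm difference at T1 caused by knowing the arm, in SD units. Assume it is present at T1 and gone by T5.

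- Group-by-time estimate = (T5 difference) − (T1 difference), so its bias is −s.
- Baseline-adjusted estimate = (T5 difference) − β × (T1 difference), so its bias is −βs.

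The documents give neither s nor β. Assumed ranges:

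| s (SD) | Group-by-time bias, size | Share of 0.30 | Adjusted bias, β = 0.5 | Adjusted bias, β = 0.3 to 0.7 |
|---|---|---|---|---|
| 0.05 | 0.05 | 17% | 0.025 | 0.015 to 0.035 |
| 0.10 | 0.10 | 33% | 0.05 | 0.03 to 0.07 |
| 0.20 | 0.20 | 67% | 0.10 | 0.06 to 0.14 |

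The direction depends on which arm reacts and how. If the intervention arm's T1 ratings rise relative to control, the effect is understated. If they fall, it is overstated.

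The T1-only assumption matters. If the reaction persisted in full to T5, it would cancel from the group-by-time estimate (s − s = 0), and the adjusted estimate would move by s − 0.5s = 0.5s in the other direction.

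**The case against.** The strongest case against is that the exposed comparisons are secondary. Section 2.6.2 calls them exploratory, and the limitations section already acknowledges self-report and lack of blinding. Pathway Tool acceptability is collected at T2 in the intervention arm only and summarised as a single proportion, so it has no baseline and no contrast between arms. The Flourishing Check ratings are not compared between arms either, and the note to Table 1 sends their analysis to a separate paper. All of this stands and limits the severity, although Table 3 still uses the Flourishing Check ratings for progression.

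A reader might also infer more than the documents support:

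- **That parents are certainly told their arm before T1.** The email has no stated day. Its place is read from sentence order, in a paragraph that is not strictly chronological.
- **That records with missing key variables are deleted, contradicting the missing-at-random handling.** Section 2.5 says such records are flagged. Removal is an inference, detailed rules may sit in a fuller document, and Section 2.6.2 keeps incomplete outcome data. No conflict is shown.
- **That the screeners know the arm.** This is not stated. What can be said is that no masking is stated.
- **That dropout before T1 destroys the 2:1 balance.** Assumed losses of 5% and 15% would leave 400 × 0.95 = 380 and 200 × 0.85 = 170, a ratio of 2.24:1. The rates have no source, and an altered ratio is not in itself a bias. The larger T1 gift card (40 AUD, against 20 AUD at the other timepoints) also works against such loss.
- **That no likelihood method could repair the loss.** Loss that depends only on arm and modelled covariates is missing at random. Only dependence on unobserved outcomes is beyond repair, and different loss rates alone do not show that.

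**Conclusion.** The point holds as a sequencing weakness. Randomisation precedes T1, nothing withholds the arm until T1 is submitted, and the T1 scores then enter the between-arm models both as a time level and as a covariate. Bias is possible but not demonstrated. Under an assumed T1-only shift of 0.05 to 0.20 SD, the group-by-time estimate moves by 0.05 to 0.20 SD. A baseline-adjusted estimate moves by 0.025 to 0.10 SD at an assumed slope of 0.5. Allocation-dependent removal of records is a further possibility, because response-based screening comes after allocation without stated masking.

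This should be fixed, but it is not a fatal flaw. No stated sample-size figure is wrong, and the Pathway Tool acceptability proportion is not a between-arm estimate. The case for acting is that the change is cheap and that a baseline given after disclosure cannot be retaken.

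**What to change.** - Trigger the REDCap randomisation when T1 has been submitted and the automated T1 checks are passed. Take child age, gender and locality, the stratification factors, from the screening form.
- At minimum, if randomisation stays where it is, withhold the allocation email until T1 is submitted.
- Then send the allocation email and release the Pathway Tool link to the intervention arm. The tool opens only after the Flourishing Check, itself a T1 item, so the design does not need allocation any earlier.
- Do any later manual screening masked to arm.
- Analyse all randomised parents. Use exclusions for later validity failures only as a sensitivity analysis, and report exclusions by arm.
- Amend Sections 2.1, 2.2.1 and 2.5 and Table 1 to show the new order.

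The cost is a small REDCap workflow change and a short amendment, with allocation slightly later than the eligibility form. Using only the automated checks as the gate avoids delaying tool access for manual review. The sample-size figures do not change. The reordering does not remove any effect of knowing the arm on the T5 self-ratings, which remains a limitation of an unblinded trial.
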